#### Statistical methods

2.6.1

We will use a paired t-test for the primary endpoint as we measure insulin sensitivity M and M/I values from the same individuals before and after taking POA vs placebo. However, given the relatively small sample size of the study, which raises the possibility of results not being normally distributed, we will also use Wilcoxon non-parametric test to compare two paired groups (before and after, POA vs placebo). The focus of these analysis will be insulin sensitivity; however, we will use multivariate regression analysis, which also provides the flexibility of controlling for and evaluating covariates such as age, sex, sleep, and BMI. We will apply the same testing to all endpoints. According to some association studies, we expect to see a higher magnitude of the POA effect in women. We will aim for study enrollment to be at least 50% women to be able to detect sex differences in the POA effect.

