#### Sample size and power

2.6.2

The study is powered only for the primary endpoint, insulin sensitivity. We expect a mean insulin sensitivity-M value (measured as steady state clamp glucose infusion rate) of approximately 7.5 ± 1.7 mg/kg/min with placebo, based on previous clamp studies^30^. Based on previous human studies, we expect to see at least a 20% difference between placebo vs. POA treatments. A sample size of 40 subjects with complete data will provide greater than 80% power for these assumptions. We will perform stratified randomization based on subjects’ BMI (<30>), and gender for homogenous treatment groups. 3:2 POA vs placebo assignment will allow us to achieve this randomization goal. We were also implementing oral glucose tolerance test results for the additional stratification of the randomization, however additional invasive testing before starting the trial period caused scheduling conflicts and compliance problems. Hence, we have discontinued OGTT for the stratification criteria.

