### Expected outcome

3.1

The primary endpoint of this study is insulin sensitivity which will be evaluated by the hyperinsulinemic euglycemic clamp and estimated by the HOMA-IR. The secondary endpoints demonstrated in **Table 6** are glucose and c-peptide measurements performed after the modified mixed meal tolerance test, liver fat quantification, total body fat mass and body composition evaluated by DEXA scan, serum levels of fasting glucose, insulin, c-peptide, liver function tests, fasting lipid panel, hsCRP, circulating inflammatory cytokines (TNF-a, IL1-B, IL-6), FABP4, glucagon, POA, free fatty acids, glycerol, adiponectin, and leptin. We expect POA compared to placebo to improve insulin sensitivity, glucose tolerance, hepatosteatosis, whole-body fat mass, serum profile of lipids, and inflammatory markers. Additionally, we anticipate a higher therapeutic impact of POA in women compared to men.

**Table 6 T6:** Outcomes.

**Primary Endpoint**	Insulin sensitivity, evaluated by hyperinsulinemic euglycemic clamp (gold standard test), and estimated by the HOMA-IR
**Secondary Endpoints**	Liver fat quantification (evaluated by liver MRI-PDFF)
	Modified mixed meal tolerance test (standardized evening mixed meal response)
	Total body fat mass and body composition (will be evaluated by DEXA scan)
	Serum; fasting glucose, insulin, C-peptide, LFTs, fasting lipid panel, hsCRP, circulating inflammatory cytokines (TNFa, IL1-B, IL6), FABP4, glucagon, POA, free fatty acids, glycerol, adiponectin, leptin, and cortisol.

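### The target of at least 50% women is said to let the trial detect sex differences in the POA effect, but on the plan's own inputs 40 participants cannot do that reliably.

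*Protocol article*

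**What the plan says.** Statistical methods (2.6.1) states an expectation drawn from association studies: "we expect to see a higher magnitude of the POA effect in women". It then sets the enrolment target and gives its purpose: "We will aim for study enrollment to be at least 50% women to be able to detect sex differences in the POA effect". Expected outcome (3.1) repeats the expectation: "we anticipate a higher therapeutic impact of POA in women compared to men".

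Sample size and power (2.6.2) opens with a limit: "The study is powered only for the primary endpoint, insulin sensitivity". Its inputs are a clamp M value of "approximately 7.5 ± 1.7 mg/kg/min with placebo", an effect described as "we expect to see at least a 20% difference between placebo vs. POA treatments", and unequal allocation ("3:2 POA vs placebo assignment will allow us to achieve this randomization goal"). Its conclusion is "A sample size of 40 subjects with complete data will provide greater than 80% power for these assumptions". Randomization is stratified by BMI and sex.

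The article gives neither a size for the sex difference nor a power figure for it. The caution about limited numbers in Pitfalls and alternative approaches (3.3) concerns secondary endpoints and does not mention the sex comparison.

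**The concern.** The sentence in 2.6.1 gives the enrolment share a purpose: it is meant to make a difference in effect between women and men detectable. Whether it does depends on the precision of a treatment-by-sex interaction, which is a difference between two treatment differences. With the sample split evenly by sex and the same allocation in each sex, the standard error of that contrast is twice that of the overall treatment effect. A sample sized for the overall effect will therefore seldom have useful power for an interaction of similar or smaller size.

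The interpretation of the sex result is at stake. The article announces in advance that women should benefit more and says the trial can show it. A reader who accepts that could take an inconclusive interaction as evidence that the sexes respond alike, when the estimate is simply imprecise. The primary comparison is not affected.

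**Working it through.** **Inputs from the article (2.6.1 and 2.6.2).** N = 40 with complete data; SD 1.7 mg/kg/min; placebo mean 7.5; effect 20% × 7.5 = 1.5 mg/kg/min; allocation 3:2, so 24 POA and 16 placebo. At exactly 50% women each sex has 12 POA and 8 placebo.

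**Assumptions, because the article is silent.** Alpha 0.05 two-sided; a sex difference in effect of 1.0 to 1.5 mg/kg/min; SD 1.7 as the residual SD, with baseline adjustment tried as a variant.

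**Step 1: the plan's own power figure.** SE of the overall effect = 1.7 × √(1/24 + 1/16) = 0.549. Power for 1.5 is 78% by the normal approximation and 76% by the noncentral t (38 df). One-sided testing at 0.05 gives 85%, and baseline adjustment with correlation 0.6 gives 91%. The stated figure of more than 80% is therefore close to, or met under, reasonable readings.

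**Step 2: SE of the interaction.** 1.7 × √(1/12 + 1/8 + 1/12 + 1/8) = 1.7 × 0.6455 = 1.097 mg/kg/min, which is 2 × 0.549.

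**Step 3: detectable difference.** By the normal approximation, 80% power needs (1.96 + 0.84) × 1.097 = 3.07. The noncentral t with 36 df gives 3.16. Relative to the assumed overall effect, 3.16 / 1.5 = 2.1.

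**Step 4: power for given sex differences (noncentral t, 36 df, SD 1.7).**

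| Sex difference in effect (mg/kg/min) | Example, women vs men | Power |
|---|---|---|
| 1.0 | 2.0 vs 1.0 | 14% |
| 1.5 | 2.25 vs 0.75 | 27% |
| 2.0 | 2.5 vs 0.5 | 43% |
| 3.0 | 3.0 vs 0 | 76% |

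The examples average to the assumed overall effect of 1.5.

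**Step 5: sensitivity, for differences of 1.0 and 1.5.**

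| Variant | 1.0 | 1.5 |
|---|---|---|
| Baseline correlation 0.6: SD 1.7 × √(1 − 0.36) = 1.36 | 20% | 38% |
| Baseline correlation 0.7: SD 1.7 × √(1 − 0.49) = 1.21 | 24% | 46% |
| One-sided 0.05, unadjusted | 23% | 38% |
| 1:1 allocation, unadjusted | 15% | 27% |
| 70% women, unadjusted | 13% | 23% |

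The last row shows that going beyond 50% women, which the target allows, lowers power for this comparison.

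**Step 6: what 80% power would take.** At SD 1.7, a difference of 1.5 needs about 169 participants and a difference of 1.0 about 379 (normal approximation). With 40 participants and a difference of 1.5, the residual SD would have to be about 1.5 / (2.80 × 0.6455) = 0.83. That corresponds to a baseline correlation of √(1 − (0.83/1.7)²) = 0.87.

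**The case against.** The strongest reply is that the sentence is an enrolment aim and not a power claim. It carries no effect size or power figure, and the next section confines formal power to the primary endpoint. An even split by sex is also the best choice for this comparison at a fixed sample size. Part of this stands: the limit in 2.6.2 softens the sentence. It does not withdraw it, because the sex comparison concerns that same endpoint and 2.6.1 still names detection as the purpose of the target.

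A second reply is that 14% to 27% is the low end. That also stands. The sex difference of 1.0 to 1.5 is my assumption. The SD of 1.7 describes variation between people, whereas M is measured before and after treatment in each participant. Baseline adjustment raises the range to about 20% to 46%, which is still below one half.

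Three stronger readings are tempting, and the article does not support them.

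- A reader might infer that the plan has no means of testing an interaction. The planned regression evaluates sex among its covariates and could hold the term, and a condensed article may leave such detail to the full protocol or analysis plan.
- A reader might infer that separate tests within each sex will be used to claim a difference. No section plans this.
- A reader might infer that the overall comparison is itself underpowered. That depends on the unstated alpha and on ignoring the baseline measurement.

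**Conclusion.** The point holds, limited to the stated ability to detect sex differences. On the article's N, allocation and SD, with a two-sided alpha of 0.05 assumed, only a sex difference of about 3.2 mg/kg/min would be found with 80% power. Even an effect of 3.0 in women and none in men falls slightly short without adjustment. The exact power cannot be fixed, because the article gives neither the size of the sex difference nor the baseline correlation. For differences up to 1.5 it stays below 50% in every variant tried.

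The matter deserves correction but is modest: one sentence claims a property that the design lacks, and 2.6.1 and 2.6.2 need to be reconciled. It says nothing against the primary analysis, the sample size for the overall comparison, or the enrolment target itself.

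**What to change.** In 2.6.1, replace the purpose given for the enrolment target with: *Sex differences in the POA effect are exploratory; the trial is not powered to detect them.* Keep the target, justified by balance and representativeness. State that the sex difference will be reported as a treatment-by-sex term in the regression already planned in that section, as an estimate with a 95% confidence interval. Without adjustment the interval would reach about 2.03 × 1.097 = 2.2 mg/kg/min either side, which shows readers how little the trial can say on this question. Word the expectation in 3.1 to match.

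The cost is one changed sentence, one extra model term, and the loss of a claim of detectability. No participants or procedures are added, and the primary test is unchanged.

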#### Sample size and power

2.6.2

The study is powered only for the primary endpoint, insulin sensitivity. We expect a mean insulin sensitivity-M value (measured as steady state clamp glucose infusion rate) of approximately 7.5 ± 1.7 mg/kg/min with placebo, based on previous clamp studies^30^. Based on previous human studies, we expect to see at least a 20% difference between placebo vs. POA treatments. A sample size of 40 subjects with complete data will provide greater than 80% power for these assumptions. We will perform stratified randomization based on subjects’ BMI (<30>), and gender for homogenous treatment groups. 3:2 POA vs placebo assignment will allow us to achieve this randomization goal. We were also implementing oral glucose tolerance test results for the additional stratification of the randomization, however additional invasive testing before starting the trial period caused scheduling conflicts and compliance problems. Hence, we have discontinued OGTT for the stratification criteria.

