### Study design and setting

2.1

This is a prospective, single-center, 8-week, double-blind, randomized, placebo-controlled clinical trial (NCT05560971) enrolling 40 individuals with a prediabetes and BMI of 25-40 kg/m^2^. Study participants will be recruited at Brigham and Women’s Hospital in Boston, Massachusetts, USA with the inclusion and exclusion criteria provided in **Table 1**. **Figure 2** shows a description of the enrollment and evaluation procedures. The protocol of this study was approved by the Institutional Review Board of Mass General Brigham. This investigator-initiated study is funded by Tersus Life Sciences, LLC, protocol no: 2022P001764.

**Table 1 T1:** Eligibility criteria.

**Inclusion Criteria**	Age 18 to 70 years with BMI 25-40 kg/m^2^
	Overweight and obese individuals with insulin resistance, prediabetes and/or impaired glucose tolerance HbA1c between 5.6-6.5, Impaired fasting plasma glucose (>99, ≤126 mg/dL), or HOMA-IR value above 2.5.
		BP <150/90 with or without medication, GFR>60, ALT, AST <300, TSH within normal ranges with or without medication
	**Exclusion Criteria**		Pregnancy or breastfeeding
			Use of any medications (except thyroid hormone with normal TSH, anti-hypertensives with blood pressure <150/90, and rescue inhalers for asthma)
		Use of OTC supplements (except vitamin D), avoiding supplements containing lipid supplements (e.g., fish oil macadamia oil, cod liver oil, krill oil, flaxseed, sea buckthorn oil) within 3 months of study participation is ensured	
Greater than 3 servings/day combined of cheese, milk, kefir, or yogurt for the last 3 months before the study	
Diagnosed with any type of diabetes mellitus and/or taking glucose-lowering medications	
Recent weight loss (more than 7% of TBW in last 3 months)	
Established major chronic diseases such as major cardiovascular disease (history of myocardial infarction, stroke, heart failure, coronary artery bypass graft, arrhythmia, peripheral arterial disease), bleeding disorder or anticoagulation use, active cancer, end-stage renal disease, proteinuria (>3g/day), dementia, severe chronic obstructive pulmonary disease (needs systemic steroid therapy), significant liver disease (ALT-AST>300)	
History of ongoing smoking cigarettes >1 pack/day, alcohol abuse, or drug abuse	
Treatment with any investigational drug in the one month preceding the study	

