
While designing translational studies, one of the most important aspects is safety. Unsaturated fat, namely POA, has beneficial effects on glucose metabolism, whereas the same amount of saturated fat, namely palmitic acid, is detrimental (22, 44). This concept has been proven by investigating the dietary habits of Greenland Eskimos in the 1970s. Their diet consisted of 55% fat enriched with POA (3 times higher than a Western diet, an average of 6.54 grams/day), which surprisingly resulted in significant protection from diabetes, dyslipidemia, and coronary heart disease as compared to Eskimos living in Denmark, who were consuming a Western diet (87, 88). POA is the second most abundant monounsaturated fatty acid within the standard American diet (89). The average Western diet consists of approximately 2 grams of POA (90). Human intervention studies have documented the consumption of up to 15.3 g of POA/day for the duration of up to four weeks, with no serious adverse effects reported (48). According to an expert panel, 5 g POA/d (as 10 g of either Provinal® EE or TG) for the average user and 10 g POA/d (as 20 g of either Provinal® EE or TG) for a 90th percentile user is Generally Recognized as Safe (GRAS) (91). 1512 mg of pure palmitoleic acid will be given to the treatment arm in our study. The available evidence suggests that consumption of POA within the specified intake levels does not result in any significant adverse effects.

To date, there are no clinical trials that have assessed the impact of supplementation with pure POA versus placebo on glucose tolerance and insulin resistance in humans. The proposed randomized, placebo-controlled study will address this gap in knowledge, and give us an opportunity to possibly translate our basic science discovery to humans. Here we hypothesize that we can mimic the rescue mechanism of adipose tissue against obesity by supplementing high dose POA exogenously, which will improve whole-body insulin sensitivity and ameliorate hepatosteatosis.

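### The claim of more than 80% power is not supported by the inputs given with it: a conventional two-sided 5% comparison at 3:2 has about 76%, and enrolling 40 leaves no allowance for loss

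*Protocol article*

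**What the plan says.** Section 2.6.2 of the protocol article expects an M value of "approximately 7.5 ± 1.7 mg/kg/min with placebo, based on previous clamp studies". For the effect it says "we expect to see at least a 20% difference between placebo vs. POA treatments". It then concludes: "A sample size of 40 subjects with complete data will provide greater than 80% power for these assumptions". The same section stratifies randomization by BMI and gender to obtain homogeneous groups, and adds: "3:2 POA vs placebo assignment will allow us to achieve this randomization goal".

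Section 2.1 describes the trial as "enrolling 40 individuals with a prediabetes" and a BMI of 25 to 40. That is the number enrolled, not the number completing.

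Section 2.6.1 names a paired t-test on M and M/I before and after treatment, a Wilcoxon test, and a regression that can include covariates. The article gives no alpha, sidedness, power formula, SD of change, week-0 to week-8 correlation or expected loss.

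**The concern.** The power statement is tied to its own inputs: a placebo mean, a cross-sectional SD, a percentage difference between arms and a number of completers. Those describe a comparison of two groups. Put into the usual two-sided calculation, they fall short of 80% at the stated ratio, and also at 1:1. The number enrolled equals the number required with complete data, so any dropout or failed clamp takes the trial below the number on which the claim rests.

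The figure is relied on elsewhere. Section 3.3 presents the trial as powered for clamp insulin sensitivity and contrasts this with secondary endpoints for which 40 may be too few. A null clamp result would therefore be read as having had more than an 80% chance of detecting a 20% effect, which the stated inputs do not show.

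**Working it through.** **Inputs from section 2.6.2.** Placebo mean 7.5, SD 1.7 mg/kg/min; difference 20% of 7.5 = 1.5 mg/kg/min; 40 completers at 3:2, so 24 POA and 16 placebo.

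**Assumed, because the article does not give them.** Two-sided alpha 0.05; equal SD in both arms; unadjusted comparison of week-8 values. Loss and correlation are varied below.

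**Formula.** SE = SD × √(1/n₁ + 1/n₂), and ncp = difference / SE. The t-test power comes from the noncentral t distribution with n₁ + n₂ − 2 degrees of freedom. The normal approximation is Φ(ncp − 1.96).

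**1. Attempt to reproduce the stated figure.**
- 24:16: SE = 1.7 × √(1/24 + 1/16) = 0.549; ncp = 1.5/0.549 = 2.734. With 38 df the critical value is 2.024.
- 20:20: SE = 1.7 × √(1/20 + 1/20) = 0.538; ncp = 2.790.

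| Completers (POA:placebo) | t-test, two-sided 5% | Normal approximation, two-sided 5% | t-test, one-sided 5% |
|---|---|---|---|
| 24:16 | 75.9% | 78.1% | 85.1% |
| 20:20 | 77.6% | 79.7% | 86.3% |

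The closest two-sided match to 80% is 1:1 by the normal approximation (79.7%), which is not the stated ratio. None of the four two-sided figures exceeds 80%. The 3:2 ratio costs 77.6 − 75.9 = 1.7 points by the t-test.

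**2. What the trial can detect with 80% power** (two-sided 5%, t-test).
- 24:16: 1.58 mg/kg/min, and 1.58/7.5 = 21.0%.
- 20:14: 1.71 mg/kg/min, and 1.71/7.5 = 22.8%.
- For a difference of 1.5, 80% power needs 44 completers at 26:18 (80.3%), or 45 at exactly 3:2 (27:18, 80.9%).

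**3. Loss from the 40 enrolled** (rates assumed; same t-test).
- 10% lost, 36 completers at 22:14: ncp 2.581, power 70.8%. Keeping the ratio at exactly 3:2 gives 71.2%.
- 15% lost, 34 completers at 20:14: ncp 2.532, power 69.0%. Keeping the ratio at exactly 3:2 gives 68.6%.

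**4. Using the baseline clamp** (correlation ρ between week 0 and week 8 assumed; SD 1.7 at each visit; 24:16). The SD becomes 1.7 × √(1 − ρ²) for the baseline-adjusted model and 1.7 × √(2(1 − ρ)) for change scores.

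| ρ | Baseline-adjusted | Change score |
|---|---|---|
| 0.3 | 79.8% | 61.5% |
| 0.5 | 86.8% | 75.9% |
| 0.7 | 96.2% | 93.0% |

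The adjusted model passes 80% at ρ of about 0.31 and reaches 81% at 0.35. The change-score comparison passes 80% at about 0.55. With 34 completers (20:14), the adjusted model gives about 81% at ρ = 0.5.

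**The case against.** The best defence is that 76% is the power of an analysis the article does not name. Section 2.6.1 plans paired tests and regression, both of which can use the baseline clamp, and alpha and sidedness may sit in a fuller document that is not shown. With 40 completers and a moderate correlation, a baseline-adjusted comparison exceeds 80%. A paired test within the 24 POA participants, for a change of 1.5, would have 83% power even at zero correlation. The effect is put as at least 20%, and 22% would give 83% at 24:16. Reading the 20% relative to the POA mean (7.5/0.8 − 7.5 = 1.875) would give 91.5%. By the normal approximation the shortfall is about 2 points at 3:2.

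Much of this stands. A reader might infer that the trial cannot have 80% power, or that only a one-sided test could rescue the claim. The documents support neither, because the baseline-adjusted model can also exceed 80%. The defence does not make the sentence correct, however. The claim is made for the listed assumptions, and these contain no correlation or SD of change. Using the baseline can also lower power, as the change-score column shows. The within-arm paired test does not compare POA with placebo. The 20% is attached to a stated placebo mean, so 1.5 is the natural reading.

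The 10 to 15% loss is an illustration and not a figure from the article. That 40 are enrolled and 40 are needed complete does not depend on it.

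A reader might also see a contradiction between taking the 20% from previous human studies and the Discussion's remark that "there are no clinical trials that have assessed the impact of supplementation with pure POA versus placebo on glucose tolerance". That remark denies only earlier trials of pure POA against placebo. The article describes human studies with other POA sources and association studies, one of them using clamps, so no contradiction is shown.

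**Conclusion.** The claim of more than 80% power is not supported by the inputs stated beside it. Under a two-sided 5% unadjusted two-sample comparison with 24:16 completers, power for a 20% difference is about 76% (t) or 78% (normal approximation), and 80% power is reached at a difference of about 21%. The gap is modest, and it rests on an assumed alpha and sidedness and on a between-arm comparison of week-8 values. Whether the planned analysis would exceed 80% cannot be determined from the article, because that turns on an unstated correlation or test.

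Two further points hold under any formula. Enrolling 40 while requiring 40 with complete data leaves no allowance for loss. And the 3:2 ratio does not produce balance: stratification can do that at any ratio, while 3:2 costs a little power.

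**What to change.** Change the wording of section 2.6.2; no change to the number of participants is asked for.

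1. Replace the power sentence in one of two ways:
   - State about 76% power (two-sided 5%, unadjusted t-test, 24:16 completers) for a 20% difference, with 80% power for about 21%, or about 23% with 34 completers.
   - Base the power on a baseline-adjusted between-group analysis, name alpha and sidedness, and show power over a range of week-0 to week-8 correlations, for example 0.3 to 0.7.
2. Reconcile the 40 enrolled in section 2.1 with the 40 complete in section 2.6.2 by giving power for fewer completers, with the loss rate labelled as an assumption.
3. Correct the sentence that credits 3:2 with balance: attribute balance to the stratification and, if 3:2 is kept, give its actual reason.
4. Bring the statement in section 3.3 that the trial is powered for insulin sensitivity into line with the new figure.

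The cost is a few sentences and, under the first option, a slightly less favourable power figure.
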